### Statistics

#### Sample size calculation

As this is a feasibility pilot study, power calculation for sample size determination is not an obligatory requirement [40]. The pilot study will not be powered to detect statistical differences in key clinical outcomes. We will review patient and staff feedback before finalising a protocol for a full-scale multicentre RCT.

#### Statistical analysis

To determine the feasibility, we will perform the analysis against established stop-go rules according to the CONSORT statement for pilot and feasibility trials [41]. The feasibility analysis will focus on the outcomes described above. For example, we will compute the percentage and 95% confidence intervals (CI) of IPV positive women, who consented to receive e-health package and consented to randomization in the control group, following the same analytical approach than other pilot studies [42].

#### Progression criteria

Table 1 outlines the main criteria that will be considered to assess the feasibility of a full-scale RCT. In addition, our qualitative findings will also be used to support the decision-making around progression to a full-scale trial. For example, if a progression criterion outlined in Table 1 does not meet the threshold for progression, but we have developed a qualitative understanding of why this occurred and how it could be improved, then it may still be possible to proceed with the full trial. The research team of the STOP project will have access to these interim results.

**Table 1 pone.0282997.t001:** Suggested progression criteria in eIPV trial.

Feasibility objectives and related data to be collected	Go criteria to proceed to full trial	Criteria to reassess and adjust full trial protocol	Stop criteria
Study population			
1. Consent rate of eligible women	Rate >25% of eligible women agreeing to participate.	Rate between 11% and 24% women agreeing to participate	Rate <10% of eligible women agreeing to participate
Study outcomes			
2. Proportion of women in either intervention or control group for whom the allocated treatment is adhered to.	Adherence to allocated treatment in >80% of study sample.	Adherence to allocated treatment in between 51% and 79% of study sample.	Adherence to allocated treatment in <50% of study sample.
RCT process			
3. Collection of data on clinical outcomes	Complete data available of >80% of study sample.	Missing data between 21% and 49% of study sample.	Data missing of >50% of study sample.

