**Fig 2 pone.0282997.g002:**
[figure not shown]
Flowchart of eIPV trial.

In the second stage, participants who have been assigned to the control, will be reapproached and given information about their participation in the control group. At this stage, they will be invited to accept a delay in the intervention (e-health package eight weeks later) and be asked to give the second informed consent for a delayed intervention. Those who decline will remain in the cohort study. Those in the cohort only group will not be informed about the randomization, as their subsequent follow up in the study will remain part of the cohort study to which they would already have consented in the first stage. We will substitute the women who not consent being part of the control until we reach the sample required (5 women in each country). This information will be also analysed for a future full-scale RCT.

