### Eligibility criteria

All women who fulfil the inclusion criteria will be screened and invited to receive an e-health package. Of those who accept the e-health intervention, 20 women will be randomised, 10 women in each country. In Spain and Denmark, respectively, 5 will be allocated in the intervention group and 5 will be asked to consent to be in the control group.

Inclusion criteria: pregnant women at <12 weeks gestation, who screen positive in IPV at the first antenatal visit and accept the e-health package.

Exclusion criteria: (1) women who cannot be informed about the study without their partners or other family members knowing; (2) mentally or physically incapacity to participate in the study; (3) women below 16 years in Spain or below 18 years in Denmark; (4) inability to understand Danish/Spanish, (5) lack of internet and electronic device and (6) women with extreme severity of IPV. Women selected to participate in the trial in this situation will receive an evaluation of danger before randomisation. If the severity of IPV is confirmed to be at high level of danger, these pregnant women will be routinely treated and supported according to the standard protocol in each country. Following this path, any potential risk for the women will be taken into account from the beginning of the process and women will be protected. Women who have same-sex partners will be screened, but their data will not be used for the purpose of this study.

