### Recruitment: Consent procedures

In advance, a written, informed consent (in Spain the informed consent will be oral and recorded) for administering the screening of IPV, will be sought from the pregnant women at the first antenatal visit with a midwife. Those who screen positive, will also be asked for consent to receive the e-health package intervention and to complete baseline and outcome measurement questionnaires (one month after the intervention). For the pilot trial, women who consent to receive the e-health package will be randomized (following a modified Zelen’s design) into the intervention group (without their knowledge) or into the control group. Women in the control group will additionally be asked for a second informed consent, to be allocated in this group and to receive the e-health package 8 weeks later. This approach is suggested by the input of IPV survivors. A few women from the intervention and control groups of the pilot trial will be asked for consent to be contacted for a qualitative interview. Women will be informed that they have the right to refuse participation as well as to withdraw their consent at any time, without giving a reason, and that this will not affect their subsequent care. If they withdraw consent, data collected up to the point of withdrawal will be retained in the study. Participant information sheets and consent forms used for this pilot study are available on request from investigators. The informed consent provides study aims, contact details and sources for further information. Given the importance of taking into consideration the views and opinion of the participants [25], all recruitment materials have been developed with significant input from a patient and public involvement (PPI) group consisting at two participant representatives from Spain and Denmark (see the Discussion section).

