### Study interventions and assessments

Intervention group: Women positive for IPV who accept the e-Health intervention and who have been randomly allocated in the intervention group will receive the e-health package as the rest of the cohort, as well as the baseline and outcome measurements. The e-health package will include six video counselling sessions by trained providers—a psychologist in Spain; midwives in Denmark. Women in both countries will be provided access to a mobile app for designing security plans. This will be an adapted version of the mobile app “My Plan”. To organize and host the video counselling sessions the platform “Linkello Medical” will be used in Spain and the app “My Hospital” will be used in Denmark. Both allow health providers to interact with the women in the place they prefer as long as they have Internet connection. In “Linkello Medical”, the psychologist will send an Internet link to the women by her preferred means (via mobile message or by email) and she would just have to click on the link to connect. Women will not need to register nor provide any personal data. The link will be volatile, i.e., it will be not reusable after completion of the communication. In “My Hospital”, is a software developed specifically for confidential hospital-patient communication in the Region of Southern Denmark and is already used in antenatal care as a regular communication tool. When the pregnant woman attend her first antenatal care visit, she will be introduced to My Hospital and instructed in how to access the system via the Internet or a mobile app. The midwives book the women for a video call through the system. Fifteen minutes before the video call is starting, the woman receives a notification to accept the call. Once the woman has accepted the call, the midwife can start the video consultation. This easy and confidential way of interaction will facilitate women’s participation. The mobile app for safety planning will be camouflaged to look like a common pregnancy app. The content and setup of the safety planning app was adapted from the interactive safety decision aid developed by Glass, et al. [26] which is freely available. A safety plan is a personal and practical plan, designed by a woman exposed to violence to minimize their risk of danger and exposure to violence. By digitalizing the safety plan into an app, the women will always have it available to remind them of their own strategies and resources. The safety planning element will be hidden inside the pregnancy app for security reasons; the women must log on for this element to be opened. Once a woman has logged on, the front page consists of two buttons, “Help” and “Emergency”. Both buttons consist of default contact information for relevant resources which can help a woman in case she needs help or is in an emergency situation. The woman can edit the information to fit her own needs. The app also includes the following features: “Warning signs”, where the woman can add signs that may trigger situations where violence could occur; “Strategies”‘, where the woman can note down her coping strategies; and, “Diary”, where a woman can write down anything of importance. It will also contain the feature “Knowledge about domestic violence” which will provide information and links to local and national resource’s relevant for women exposed to violence. Under another feature called “Quick Messages” a woman can enable a predetermined message to her emergency contacts. In case the woman needs to exit the app quickly, she will be able to press the “Quick-exit” button, where she will immediately return to the camouflaged part of the app. This app has been made freely downloadable to researchers and users for both android and iOS devices.

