Relevant concomitant care and interventions that are permitted during the trial: Women in both the intervention and control groups would be able to benefit from the standard care available for women exposed to IPV thorough the usual provision made by social and health services at any time during the study, if necessary. Indeed, one of the video-counselling sessions will be dedicated to inform women about the available resources in their community. IPV counsellors will specify if women in the intervention and the control group are in need of these resources during the time of the pilot as a valuable information for the future full-scale trial.

To accomplish the objectives, we will collect the following information:

Primary outcome:

Number of IPV positive women, who consented to receive e-health package and consented to randomization in the control group computed as a rate.

Secondary outcomes:

Number of women who consented to receive e-health package computed as a rate.Number of women in the intervention group where complete outcome data were obtained computed as a rate.Number of women in the control group where complete outcome data were obtained computed as a rate.Number of women where there was a study protocol violation computed as a rate.Recruitment duration (in days) to get the pilot sample (5 women for the intervention group and 5 women for the control group, in each country).Benefit of the intervention perceived by women through the information obtained in qualitative interviews.Perception about the duration of delay (the duration in the future full-scale trial will be determine according to the observations derived of the pilot study and the information provided in the qualitative interviews).Reasons for acceptability, non-adherence, and obstacles to recruitment, randomisation, consent and follow-up (through qualitative interviews).

Participant timeline

The participant timeline is illustrated in Fig 1.

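### On the protocol's own eligibility definition, the consent criterion reads Go when just over a quarter of control-allocated women accept the delay, and the adherence criterion does not see the refusals

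*Protocol article*

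**What the plan says.** Criterion 1 of Table 1 (Progression criteria) sets Go at "Rate >25% of eligible women agreeing to participate", reassess at 11% to 24% and Stop below 10%. Criterion 2 sets Go at "Adherence to allocated treatment in >80% of study sample", reassess at 51% to 79% and Stop below 50%.

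The Eligibility criteria admit pregnant women under 12 weeks "who screen positive in IPV at the first antenatal visit and accept the e-health package". Consent after that point concerns one arm only: "Women in the control group will additionally be asked for a second informed consent" (Recruitment: Consent procedures), for an eight-week delay. The primary outcome is "Number of IPV positive women, who consented to receive e-health package and consented to randomization in the control group computed as a rate"; its denominator is not written out.

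The second stage of Trial design says what follows a refusal: "Those who decline will remain in the cohort study", and "We will substitute the women who not consent being part of the control until we reach the sample required (5 women in each country"). The cohort is treated without delay: intervention women "will receive the e-health package as the rest of the cohort" (Study interventions and assessments). The same section moves the data of a control who later asks for immediate treatment into the cohort study.

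**The concern.** In this modified Zelen design the second consent is not an ordinary recruitment rate. It is asked after allocation, of controls only, and refusing it means having the package straight away. The acceptance rate p is therefore the share of the allocated control arm that experiences the control condition at all.

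A limit of 25% may be reasonable for recruiting from a screened population. Applied to p, it lets the pilot report Go on its main feasibility question when most allocated controls have left the control condition. Criterion 2 would be the natural safeguard, but substitution takes the refusals out of the sample it measures. The planners of the full trial could then read a favourable table while the comparison they intend is either heavily diluted or no longer protected by randomisation.

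**Working it through.** The protocol gives no power calculation or effect size, so there is no figure of its own to reproduce.

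**Inputs from the protocol.** Go above 25% (criterion 1); Go above 80%, Stop below 50% (criterion 2); 1:1 allocation (Randomisation procedures); five consenting controls per country, ten in all, with decliners substituted (Trial design).

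**Assumptions, not in the protocol.** Full trial analysed as randomised; decliners take up the package as the intervention arm does; for the sample-size check, two-sided 5% level, 80% power, SD 1, and undiluted differences of 0.3, 0.5 and 0.8.

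**1. What a Go looks like.** Ten consenting controls out of 39 asked is 10/39 = 25.6%, a Go on criterion 1 with 29 refusals. The exact 95% CI is 13% to 42%.

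**2. If decliners are kept as randomised.** Contrast = p × full effect, so the sample-size factor is 1/p².

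| p | 1/p² |
|---|---|
| 11% | 82.6 |
| 24% | 17.4 |
| 25% | 16.0 |
| 26% | 14.8 |
| 50% | 4.0 |
| 60% | 2.8 |
| 80% | 1.6 |

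Sample sizes for means agree. At p = 25%, n per arm rises from 175 to 2791 (difference 0.3), 63 to 1005 (0.5) and 25 to 393 (0.8), which are factors of 15.7 to 15.95. Power at the undiluted n falls from 80% to about 10%. For assumed binary outcomes of 30% v 50% and 20% v 40%, the factors are 14.8 and 13.3.

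**3. If decliners are dropped and replaced.** The analysed contrast is not diluted. The cost is 1/0.25 = 4 women allocated to control per control analysed, and a self-selected quarter of controls is set against all allocated intervention women.

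**4. What criterion 2 would show.**
- Decliners substituted out: refusal does not enter, and the criterion can read Go at any p.
- Decliners counted, pooled at 1:1, full adherence in the intervention arm: at most (1 + p)/2. At p = 25% this is 62.5%, reassess. Go needs (1 + p)/2 > 0.80, that is p > 60%. Stop cannot be reached, since (1 + p)/2 is never below 50%.
- Decliners counted, by arm: control-arm adherence is at most p. At p = 25% this is Stop; Go needs p > 80%.

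**5. If row 1's denominator is all screen-positive women.** With package uptake u, and counting the women allocated to control, the rate is u × p. A rate of 25% then means p = 0.25/u: 50% (factor 4) at an assumed u of 50%, or 83% (factor 1.4) at an assumed u of 30%.

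**6. If row 1 means package uptake alone.** No row of Table 1 then carries the primary outcome.

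**The case against.** The strongest reply is that criterion 1 is not shown to be the second-consent rate. Its wording mentions neither controls nor delay, and Screening procedures uses the word eligible for women who have not yet been screened. That ambiguity is real, and the size of the problem depends on it (steps 5 and 6). It does not remove the problem, because the alternative reading as package uptake leaves the primary outcome without a limit. The eligibility definition also supports the second-consent reading, as does Statistical analysis, which uses control-group consent as its example of what is judged against the stop-go rules.

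A reader might go further and infer that Table 1 as a whole approves a trial needing sixteen times the women. The documents do not support that. They fix no analysis set for the full trial, and an all-Go table coincides with the sixteen-fold factor only if the pilot excludes decliners and the full trial includes them.

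A reader might also say that rows 1 and 2 contradict each other. They are separate gates on separate quantities, and they conflict only if decliners count in row 2, which the protocol does not say. Nor should one put pooled adherence at 20/50 = 40% (Stop): that sets 10 intervention women against 40 controls and ignores the 1:1 allocation.

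Finally, the criteria are labelled as suggested, qualitative findings will be weighed, and data on refusals will be analysed for the full trial. So a low p would be visible. But the example given under Progression criteria shows how a missed threshold may be overridden, not how a passed one may be vetoed.

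**Conclusion.** The point stands in conditional form and should be fixed. On the protocol's own eligibility definition, criterion 1 alone reads Go at p just above 25%, and criterion 2 does not catch it because decliners are replaced. The consequence depends on a choice the protocol leaves open. Kept as randomised, with equal uptake of the package, the full trial faces a factor of about 15 to 16 near the limit. Dropped and replaced, it faces a self-selected control group and about four controls allocated per one analysed. On the package-uptake reading, the primary outcome has no progression limit. A change to Table 1 is needed on each of these readings.

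**What to change.** - State the denominator of criterion 1, and keep its 25% and 10% limits only for package uptake among screen-positive women.
- Add a row for second consent, defined as women accepting the delay divided by controls invited. Report it with its 95% CI and the implied factor 1/p².
- In criterion 2, count women who decline the delay as non-adherent to their allocation, and apply the existing 80% and 50% limits separately by arm. If the sponsor prefers a pooled figure, say so and note that Go then corresponds to p above 60% at best. The sponsor may justify other limits.

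The cost is one table row and a sentence or two of analysis, with no extra women or data. The downside is a less favourable Go limit, judged on an imprecise estimate: with ten acceptors, 10/20 has an exact 95% CI of 27% to 73%, and 10/12 has 52% to 98%.

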### Randomisation procedures

The research team will consult the data server on a daily basis to identify women who screen positive in IPV and accept to receive the e-health package to randomly allocate them (using a computer-generated random numbers) in the intervention or control group through randomisation at a ratio of 1:1. IPV counsellors will be informed of the assignments to each group. Women in the intervention group will be blinded but not women in the control group.

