Prior to performing a large interventional trial, a pilot study is needed to identify barriers to recruitment, assess feasibility and acceptability of the treatment, and fine-tune study procedures. No RCT has previously assessed an e-health intervention in IPV among pregnant women in comparison with a control group (with a delay intervention). In this pilot trial, we chose to perform randomisation with a modified Zelen’s design rather than simple randomisation for several reasons. Participants who take part in standard RCTs will make a judgment of their preferred treatment and often expect to be allocated to the treatment group [44]. If this does not occur, it can be followed by dissatisfaction and distrust in those who approached them to take part [45]. Consequently, randomization to a control group may lead to dropout after allocation. The original Zelen design involves randomization before consent, with consent only required from those allocated to the intervention, whereas the control group receive their usual care [24]. Baseline data and outcomes are collected from medical records (with ethical approval). However, it is not possible to have interaction with the control group during follow-up, as they are not informed of their presence in a study. Taking all of this into consideration, we hypothesized that women will accept the intervention because they perceive that it is needed for their support and protection. If they perceive it like this, they may not want to be randomized into control group or they may drop out after been randomized to usual care instead of intervention. To overcome this difficulty with acceptance of allocation to the control group, we followed the input of IPV survivors in a focus group we conducted [13]. Amongst other things the survivors informed us that they would prefer delayed intervention instead of usual care in a control group. The opinion of the participant representative in our project affirmed their support for this approach. A systematic review concluded that a delayed intervention could be an effective way of minimizing dropout [46]. In our pilot, thus we chose to offer to women of the control group a delay in the intervention. It is this specific challenge that is addressed in our pilot study. We wish to estimate the rates of acceptance of randomization primarily. We do not aim to estimate effect sizes. The approaches recommended for use of standardized effect sizes for pilot study sample sizes estimation are not applicable [47]. Our analytic approach will compute simple statistic with 95% CI and we will employ qualitative judgment in assessing the need to prepare a full-scale RCT.

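### Progression criteria 2 and 3 are judged on both arms pooled, so an arm in the Stop band can read as Reassess and, at 10 per arm, total failure of one arm does not trigger Stop

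*Protocol article*

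**What the plan says.** The Progression criteria section of the protocol article gives three criteria in Table 1. Criterion 2 is the "Proportion of women in either intervention or control group for whom the allocated treatment is adhered to". Its bands are Go above 80%, Reassess from 51% to 79% and Stop below 50%, each as a share of the study sample. Criterion 3 reads Go when there is "Complete data available of >80% of study sample", Reassess when 21% to 49% of the sample have missing data, and Stop when more than 50% do. No cut-off in either row is set by arm.

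The sample is fixed under Eligibility criteria: "Of those who accept the e-health intervention, 20 women will be randomised, 10 women in each country", and in each country "5 will be allocated in the intervention group and 5 will be asked to consent to be in the control group". Women are placed "in the intervention or control group through randomisation at a ratio of 1:1" (Randomisation procedures). Under Trial design, women who decline the control allocation are replaced until each country has its five controls.

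The outcome list under Study interventions and assessments separates completeness by arm. One entry is "Number of women in the control group where complete outcome data were obtained computed as a rate", and there is a matching entry for the intervention group. It has no entry for adherence by arm. The Discussion gives the reason for the pilot: "Consequently, randomization to a control group may lead to dropout after allocation".

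**The concern.** Adherence is a different behaviour in each arm. In the intervention arm it is taking part in six video sessions planned every two weeks. In the control arm it is going without them for eight weeks. An average of the two describes neither. The failure that the pilot is meant to detect, women leaving after allocation to control, belongs to one arm, and a pooled percentage lets a good result in the other arm offset it.

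A full trial needs both an acceptable programme and a control arm that stays, and unequal loss between arms would threaten its comparison. A progression rule that does not react when one arm fails gives a misleading reading on that question.

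**Working it through.** **Inputs.** Two countries with 5 + 5 women each give 2 × 10 = 20, which reproduces the stated sample: 10 intervention and 10 control. The cut-offs are those of Table 1.

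**Cut-offs as counts.**

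| Band | Pooled, n = 20 | Same cut-offs on one arm, n = 10 |
|---|---|---|
| Go (>80%) | 17 or more | 9 or 10 |
| Reassess (51–79%) | 11 to 15 | 6 or 7 |
| Stop (<50%) | 9 or fewer | 4 or fewer |

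Criterion 3 gives the same counts when read as complete data. Exactly 50% and exactly 80% fall in no band, and both can occur. That is a separate point.

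**One arm at 10/10, the other varying.** Pooled rate = (10 + b)/20.

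| Other arm, b/10 | Pooled | Pooled reading | That arm alone |
|---|---|---|---|
| 7/10 | 17/20 = 85% | Go | 70%, Reassess |
| 6/10 | 16/20 = 80% | no band | 60%, Reassess |
| 4/10 | 14/20 = 70% | Reassess | 40%, Stop |
| 1/10 | 11/20 = 55% | Reassess | 10%, Stop |
| 0/10 | 10/20 = 50% | no band | 0%, Stop |

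The last row applies to both criteria: 50% adherent is not below 50%, and 50% missing is not above 50%. For criterion 3, the 7/10 row is a Go with a 30-point difference in completeness between arms.

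**How far the offset goes.** Pooled Go needs 17/20, so the weaker arm must have at least 17 − 10 = 7. An arm observed at 4/10 or fewer therefore never gives Go. Take one given arm at 0 to 4 and the other anywhere from 0 to 10, which is 5 × 11 = 55 combinations. The pooled reading is Stop in 40, Reassess in 10 and no band in 5.

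**How often, under assumed true rates.** The article gives no expected adherence, so these are illustrations from exact binomials with 10 per arm.

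| True adherence, two arms | P(pooled Stop) | P(at least one arm at 4/10 or fewer) |
|---|---|---|
| 90% and 40% | 0.03 | 0.63 |
| 90% and 30% | 0.07 | 0.85 |
| 90% and 20% | 0.17 | 0.97 |

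**Dependence on equal denominators.** The 50% result needs 10:10. The article does not say whether women who refuse the control allocation, or who leave it and whose data pass to the cohort, count in the denominator. With 10/10 and 0/12 the pooled rate is 10/22 = 45.5% and Stop is reached. With 10/10 and 0/8 it is 10/18 = 55.6% and the masking is worse.

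**Two possible remedies, equal true adherence p in both arms.**
- Stop applied to each arm as well as pooled: a pooled total of 9 or fewer already implies an arm at 4 or fewer, so P(Stop) = 1 − [1 − P(X ≤ 4)]². At p = 0.70, P(X ≤ 4) = 0.047 and P(Stop) = 1 − 0.953² = 0.09, against 0.02 for the pooled rule. At p = 0.90 it is about 0.0003.
- Go required in each arm: P(Go) = [P(X ≥ 9)]². At p = 0.90 this is 0.736² = 0.54, against P(X ≥ 17 of 20) = 0.87 for the pooled rule. At p = 0.85 it is 0.30 against 0.65.

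**The case against.** The strongest reply is that Table 1 is not automatic. Its criteria are labelled as suggested, qualitative findings feed the decision, and the Discussion announces qualitative judgement. Completeness by arm is a listed outcome, and the Statistical analysis section says the feasibility analysis will focus on the listed outcomes, so a gap in completeness would be visible. A poor arm beside a good one usually lands in Reassess, which is a defensible response. Rates on 10 women are also noisy: 7/10 has an exact 95% confidence interval of about 35% to 93%.

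Much of this stands, and it rules out three stronger readings that a reader might infer:
- That a failing arm is hidden altogether. Completeness by arm will be reported, and an arm observed in the Stop band cannot produce Go.
- That the pilot cannot meet its objective of estimating adherence and dropout. A pooled cut-off does not prevent estimation of either rate.
- That Stop can never be reached while one arm is complete. This holds only with equal denominators, which the article does not guarantee.

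The reply leaves a gap, however. No threshold acts on the by-arm completeness rates, and adherence has no by-arm outcome at all. The only example of qualitative findings affecting a threshold is one where the trial proceeds although a criterion was missed. Nothing covers an arm that fails behind an acceptable pooled figure. Small numbers call for confidence intervals. They do not make an average of two different behaviours informative.

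**Conclusion.** The concern holds in a limited form. As written, criteria 2 and 3 can read Reassess when one arm is in the Stop band, and Go when one arm is at 70%. With 10 per arm and equal denominators, they do not reach Stop even if one arm fails completely while the other is complete. This bears on the arm-specific problem that the Discussion says the pilot addresses.

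The band results are exact counts at the planned 10:10 split and take the cut-offs as applying to the pooled sample. The word 'either' in criterion 2 is loose, but the threshold cells, which refer to the study sample, support that reading. The probabilities rest on assumed adherence rates. This is a weakness of the decision rule, and the data needed to correct it will already be collected.

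**What to change.** In Table 1:
- Define criterion 2 by arm: session attendance for the intervention arm and completion of the delay for the control arm. List adherence by arm as an outcome.
- Beside each pooled figure for criteria 2 and 3, show each arm's rate with an exact 95% confidence interval and the between-arm difference.
- Keep the pooled rule of more than 80% for Go.
- Apply the existing Stop cut-offs (below 50% adherence, more than 50% missing) to each arm as well as to the pooled sample. This cannot conflict with Go, because pooled Go already needs at least 7/10 in the weaker arm.
- State which women form each arm's denominator, including those who leave the control group.

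The cost is wording in two rows of Table 1 and one added outcome, with no new data. Each arm's rate rests on only 10 women, and the per-arm check makes Stop somewhat likelier when adherence is mediocre in both arms (0.02 to 0.09 at an assumed 70% in each). It almost never stops a sound trial (about 0.0003 at 90% in each).

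Requiring each arm to exceed 80% for Go is not recommended. It needs 9/10 in both arms and would cut the chance of Go from 0.87 to 0.54 at an assumed 90% adherence.
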